## Abstract

**Background:**

Cognitive therapy for social anxiety disorder (CT-SAD) has extensive empirical support and is recommended in several national guidelines. However, ensuring access to evidence-based psychological therapies such as CT-SAD remains a global challenge. An internet-delivered version of this treatment protocol (iCT-SAD) has recently been developed in the UK as a way to overcome this challenge, demonstrating comparable outcomes to face-to-face CT-SAD whilst requiring less therapist time per client. Initial findings also suggest its cross-cultural transferability, but the previous studies in other cultural settings used the English language programme and only included English-fluent participants as a second language. It is not yet known what outcomes can be achieved once the programme has been translated and adapted for a different cultural context. Therefore, this trial aims to evaluate the clinical efficacy of Japanese iCT-SAD when combined with treatment as usual (TAU) in clients with SAD.

**Methods:**

This two-arm, parallel-group, superiority randomised controlled trial will recruit 60 Japanese participants with SAD, randomly assigning them to either Japanese iCT-SAD + TAU or TAU alone at a ratio of 1:1. The primary outcome measure is the self-report Liebowitz Social Anxiety Scale, and secondary.outcomes include other measures of social anxiety symptoms and processes, general mood and functioning, and response to treatment. We will also assess treatment acceptability and gather participant feedback. Assessments will take place at baseline (week 0), mid-treatment (week 8), and post-treatment (week 15), with a further 3-month follow-up (week 27) for the iCT-SAD + TAU arm. The primary analyses will be conducted on an intent-to-treat basis, comparing the primary and secondary outcome measures between groups using linear mixed-effect models, along with additional mediation analysis.

**Discussion:**

Investigating the efficacy of translated and culturally adapted iCT-SAD in different cultural contexts is an important step in evaluating the global reach of internet interventions. This trial will provide valuable insights into the effects of iCT-SAD combined with usual care, and how this treatment could be delivered in routine clinical settings in Japan.

**Trial registration:**

International Standard Randomized Controlled Trials (ISRCTN), ISRCTN82859645, registered on January 19, 2024. UMIN Clinical Trials Registry (UMIN-CTR), UMIN000052702, registered on November 6, 2023.

## Administrative information

Note: the numbers in curly brackets in this protocol refer to SPIRIT checklist item numbers. The order of the items has been modified to group similar items (see http://www.equator-network.org/reporting-guidelines/spirit-2013-statement-defining-standard-protocol-items-for-clinical-trials/).

## Introduction

### Background and rationale {6a}

Social anxiety disorder (SAD) is a common and chronic mental health problem, which typically has an early age of onset, leading to a substantial negative impact on individuals’ quality of life [1]. Individual face-to-face cognitive therapy for SAD (CT-SAD) based on the Clark and Wells model [2] has extensive empirical support [3] and as a result is recommended in national guidelines in both the UK [4] and Japan [5]. Although there is evidence to suggest that people with mental health problems prefer psychological over pharmacological treatments [6], ensuring access to evidence-based psychological therapies such as CT-SAD remains a global challenge [7].

In the UK, an internet-delivered version of this treatment protocol (iCT-SAD) was developed to support wider access and dissemination [8, 9]. In order to increase the number of people receiving empirically supported psychotherapies, the National Institute for Health and Care Excellence (NICE) has conditionally recommended iCT-SAD for use in the national health service [10]. iCT-SAD is a therapist-guided internet intervention, which uses a modular structure to deliver the same treatment components as face-to-face CT-SAD. A randomised controlled trial in the UK found it to show strong efficacy, with outcomes comparable to face-to-face CT-SAD, but requiring much less therapist time per client [8]. Results of a pilot trial and randomised controlled trial in Hong Kong showed outcomes comparable to the UK trial, which suggests that it is possible to transport iCT-SAD between cultures without a substantial drop in efficacy [11, 12].

As the Hong Kong trials used the English version of iCT-SAD and included only English-speaking participants, it is not yet known what outcomes can be achieved once the programme has been translated and adapted for a different cultural context such as Japan. Initial evidence has suggested that the translation from English to Japanese has been achieved successfully, incorporating a number of small cultural adaptations where appropriate [13]. A subsequent single-arm pilot trial indicated that Japanese iCT-SAD showed good acceptability to clients and preliminary evidence of strong efficacy in Japanese clinical settings [14]. A randomised controlled trial is now warranted to evaluate Japanese iCT-SAD more robustly. The primary aim of this trial is to examine the clinical efficacy of the translated and culturally adapted Japanese iCT-SAD when combined with treatment as usual in Japanese individuals with SAD through a randomised controlled design.

## Objectives {7}

The primary objective of the current trial is to examine whether a Japanese version of iCT-SAD in combination with treatment as usual (iCT-SAD + TAU) is superior to TAU alone.

The secondary objectives are as follows:To examine whether the Japanese iCT-SAD programme is acceptable to clientsTo evaluate how the outcomes of the iCT-SAD + TAU intervention compare to previous studies of the iCT-SAD programme in the UK and Hong KongAn exploratory examination of whether baseline clinical and demographic characteristics are associated with clinical outcomes in the iCT-SAD + TAU armAn exploratory examination of candidate mediators of the relationship between treatment arm and clinical outcome

## Trial design {8}

This trial employs a two-arm, parallel-group, superiority randomised controlled design, comparing Japanese iCT-SAD in combination with treatment as usual (iCT-SAD + TAU) to TAU alone. Participants will be allocated using a 1:1 ratio. Participants will not be blinded to treatment allocation.

## Methods: participants, interventions and outcomes

### Study setting {9}

Participants will be recruited from outpatient sites at different psychiatric hospitals and clinics across Japan via referral from their primary psychiatrist. All screening and assessments will be conducted remotely or in person, and iCT-SAD will be provided on a dedicated online platform. TAU from their primary psychiatrist will be provided in person. Questionnaires for measuring outcomes and post-treatment feedback from participants will be collected online.

### Eligibility criteria {10}

The inclusion criteria for participants are as follows:Primary diagnosis of SAD based on the Diagnostic and Statistical Manual of Mental Disorders, Fifth Edition (DSM-5)Aged 18 years or overRegular, private access to an appropriate internet enable deviceResident in Japan and proficient in Japanese (written and spoken)Able to visit their primary psychiatrist regularly during the trial (at least monthly in person) for safety monitoringParticipant not currently undertaking other structured psychological therapy and agrees not to start such interventions during the trial

The exclusion criteria for participants are as follows:Current psychosis, bipolar disorder, antisocial personality disorder, or alcohol/substance use disorder (moderate or severe); this comorbidity is likely to interfere with the client’s ability to use the treatment website regularly and to process and apply the treatment contentActive suicidal ideation with intent or plan; this would indicate that immediate support is required to ensure the client’s safety and that allocation to the intervention or control arm would not be sufficient at that timePreviously received CT or cognitive behavioural therapy for SAD (defined as at least five sessions and including an exposure component); this may confound the study’s outcomes, especially with regard to iCT-SAD

### Who will take informed consent? {26a}

Informed consent will be obtained by the assessor during the eligibility assessment. Prior to this assessment, potential participants will have been sent the trial information sheet, which includes details of the purpose, design, criteria, and protection of personal information. During the eligibility assessment, potential participants will have the opportunity to ask questions about the trial. If they are happy to proceed, informed consent will be taken electronically by them submitting an online form. This form includes checkboxes for participants to state that they have received the trial information and agree to participate in the trial.

### Additional consent provisions for collection and use of participant data and biological specimens {26b}

The consent form includes permission to store an anonymised version of the dataset in an online repository. No biological specimens will be collected.

## Interventions

### Explanation for the choice of comparators {6b}

The comparator for this trial is TAU alone. TAU consists of standard psychiatric care, where participants visit their regular psychiatrist on a monthly basis. These appointments focus on mood and symptom monitoring, ongoing assessment of safety and clinical risk, and medication management. TAU was chosen as the comparator as it represents standard practice for the treatment of SAD in Japan. Japanese government regulations and implementation guidelines require that any internet-delivered intervention must be combined with regular face-to-face ambulatory care provided [15, 16]. TAU as described therefore represents an appropriate comparator for the intervention arm, which combines iCT-SAD with TAU. After the post-assessment, participants in the control arm (TAU alone) will be offered the option to receive iCT-SAD.

### Intervention description {11a}

The intervention for this trial is iCT-SAD combined with TAU (iCT-SAD + TAU) (see the above item 6b for more details about TAU). iCT-SAD is an internet-delivered therapist-guided intervention (see ‘Introduction’) [8, 9]. iCT-SAD contains eight core modules which cover key concepts on the nature and maintenance of social anxiety problems, plus 16 optional modules covering common beliefs and difficulties associated with SAD. Participants are supported to complete the core modules across the first two weeks of treatment. Subsequently, the therapist releases those optional modules that are particularly relevant to each participant’s concerns. Participants are also supported to conduct ‘behavioural experiments’, in which they test out their feared concerns in social situations whilst focussing their attention externally and dropping their safety behaviours. Trained therapists support participants by telephone, text messages, and video calls via webcam. Each telephone call lasts approximately 20 min and is used to review questionnaire measures, progress with modules and behavioural experiments, and planning for the coming week. To support initial engagement, two phone calls per week are scheduled during the first 2 weeks of treatment, followed by once-weekly phone calls until the end of the 14-week treatment phase. During the subsequent follow-up period, up to three booster calls are scheduled at monthly intervals.

### Criteria for discontinuing or modifying allocated interventions {11b}

If participants have a concern about their treatment or participation in the trial, they will be encouraged to discuss this with their therapist in the first instance. The therapist and trial team will then consider whether these concerns can be addressed through more careful tailoring of the intervention to the participant’s needs. If this is not possible and the participant wishes to withdraw from the trial, they are free to do so.

If negative events occur that require some form of urgent alternative treatment (e.g. substance misuse, deliberate self-harm, suicidal ideation or attempts), the project lead will be informed immediately to consider appropriate actions, liaising with the participant’s primary psychiatrist to arrange onward referrals.

### Strategies to improve adherence to interventions {11c}

All trial therapists have previous experience of using cognitive therapy approaches to treat SAD. They have received specialist training in iCT-SAD from an expert in this treatment protocol and have experience of treating clients using iCT-SAD from a recent pilot trial. All therapists will receive regular group supervision throughout the trial, which will include reviewing therapists’ use of the iCT-SAD site to support adherence to protocol. Monthly supervision-of-supervision will be provided by the UK team to ensure delivery is consistent with previous studies of iCT-SAD.

Participants are supported to adhere to the intervention protocol in a number of ways. Treatment begins with a more intensive phase in the first 2 weeks, supporting participants to make a strong start on their treatment, to develop engagement and motivation. Their therapist can review their progress working through treatment modules and behavioural experiments and will provide encouragement, help, and reminders as necessary. Therapists and supervisors will review participants’ activity on the iCT-SAD regularly. This provides an effective method for adherence monitoring, for example by examining whether modules or other therapy exercises have been completed.

### Relevant concomitant care permitted or prohibited during the trial {11d}

There are no restrictions on the TAU component of each treatment arm. Each primary psychiatrist will continue to provide usual treatment as clinically indicated, including medication changes if necessary. However, the initiation of other structured psychological therapy is prohibited in order to measure directly the effectiveness of iCT-SAD. All treatment changes, with the reasons for these changes, will be recorded throughout the trial period.

### Provisions for post-trial care {30}

Following trial participation, all participants will remain under the care of their primary psychiatrist, who will review their clinical needs and arrange further treatment as appropriate.

### Outcomes {12}

The principal assessment points for outcome measures will be baseline (week 0), mid-treatment (week 8), post-treatment (week 15), and 3-month follow-up (week 27, intervention arm only). The primary assessment timepoint is post-treatment (week 15).

#### Primary outcome measure

The primary outcome is a self-report version of the Liebowitz Social Anxiety Scale (LSAS) [17], one of the most widely used scales to assess the severity of social anxiety.

#### Secondary outcome measures

Secondary outcome measures will be as follows.

### Social anxiety symptoms and processes

The proportion of participants who no longer meet the SAD diagnostic criteria will be evaluated using the Anxiety and Related Disorders Interview Schedule for DSM-5 (ADIS-5) [18, 19] conducted by an independent assessor blinded to the treatment arm at the post-treatment time point. Psychological processes that maintain SAD in the Clark and Wells model [2] will be assessed using the Social Cognitions Questionnaire (SCQ), Social Behaviour Questionnaire (SBQ), Social Attitudes Questionnaire (SAQ), and Social Phobia Weekly Summary Scale (SPWSS), as described in Clark (2005) [20]. Social participation and social satisfaction will also be assessed [21].

### General mood and functioning

Depressive symptoms will be assessed with the Patient Health Questionnaire (PHQ-9) [22, 23], generalised anxiety symptoms with the Generalised Anxiety Disorder Questionnaire (GAD-7) [24, 25], and functional impairments with the Work and Social Adjustment Scale (WSAS) [26].

### Response to treatment

Response to treatment, remission from SAD, and reliable deterioration are defined using the criteria described in a pilot trial in Japan [14], which are based on previous studies of iCT-SAD [8, 9, 11, 12]. Response is defined as an improvement in the LSAS between pre- and post-treatment greater than 31%. This is comparable to an improvement subscore of 2 ‘much improved’ on the Clinical Global Impression, a psychiatric measure commonly used to define a response. Remission is defined as a decrease in the LSAS score of at least 12 points and post-treatment score of 38 points or less. Reliable deterioration is defined as an increase of at least 12 points in the LSAS score.

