### Plans to promote participant retention and complete follow-up {18b}

Participants will be in regular contact with their primary psychiatrist and/or iCT-SAD therapist, who will provide support and encouragement, and are available to discuss any concerns participants may have about treatment or trial participation. Trial information and initial assessment procedures will clarify the timescale of treatment and explain the clinical importance of receiving a full ‘dose’ of iCT-SAD. Any participants who withdraw early from either arm will be invited to complete follow-up questionnaires at the relevant remaining principal time points.

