### Adverse event reporting and harms {22}

All adverse events (AEs) and severe adverse events (SAEs), which may or may not be related to treatment, will be logged throughout the trial. Based on the guidance of Rozental et al. [33], these include the following:Worsening of SAD symptomsNegative events probably emerging from treatment perceived as adverse by the patientEmergence of new psychological symptoms unrelated to those targeted in treatment (e.g. new occurrence of insomnia, panic attacks, etc.).External negative events in participant’s life (e.g. bereavement, other stressors)Other events experienced as negative by the patient during treatment, which may or may not be related to treatment (e.g. issues related to treatment content, increased anxiety during experiments, technical issues).

SAEs are defined as negative events that occur during treatment that require some form of urgent alternative treatment (e.g. substance misuse, deliberate self-harm, suicidal ideation or attempts).

Trial therapists will identify and record their participants’ AE/SAEs when providing iCT-SAD treatment. Participants in both arms will also be asked to report any negative effects experienced during the trial, via a checklist included in the mid-, post-treatment, and 3-month FU assessment packs. AEs will be reviewed on a regular basis by the trial team, including in clinical supervision. SAEs will be brought to the project lead’s attention immediately to consider what actions may be appropriate. This would likely include contact with the participant’s primary psychiatrist*.*

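### Symptom worsening as an adverse event is detected by different routes in the two arms and is not linked to the LSAS or to the protocol's own 12-point deterioration threshold

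*Protocol article*

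**What the plan says.** **Harms.** Protocol article, Adverse event reporting and harms {22}, lists the kinds of event to be logged, with worsening of social anxiety first. No score criterion is attached. Two sources are named. The first is "Trial therapists will identify and record their participants’ AE/SAEs when providing iCT-SAD treatment". The second is "Participants in both arms will also be asked to report any negative effects experienced during the trial, via a checklist included in the" mid-treatment, post-treatment and 3-month follow-up packs.

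**Deterioration.** The section Response to treatment gives a score-based definition: "Reliable deterioration is defined as an increase of at least 12 points in the LSAS score". The sentence has no start or end visit. The two definitions before it do refer to time: "Response is defined as an improvement in the LSAS between pre- and post-treatment greater than 31" per cent, and "Remission is defined as a decrease in the LSAS score of at least 12 points and post-treatment score of 38 points or less".

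**Schedule.** Outcomes {12} sets the assessments at "baseline (week 0), mid-treatment (week 8), post-treatment (week 15), and 3-month follow-up (week 27, intervention arm only"). The LSAS is therefore due at weeks 0, 8 and 15 in both arms.

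**Early leavers.** Section {18b} states: "Any participants who withdraw early from either arm will be invited to complete follow-up questionnaires at the relevant remaining principal time points".

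**Analysis.** Section {20a} assigns Fisher's exact test to a list of categorical outcomes in which deterioration is not named separately, and leaves remaining results to description. Section {20c} plans no multiple imputation. A separate SAP is promised.

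**The concern.** Two features of the plan bear on how well this harm will be measured.

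1. **Unequal detection.** The therapist route exists only where iCT-SAD is delivered. Those therapists also go through questionnaire scores in their calls (Intervention description {11a}). For TAU alone, the harms section names the checklist and nothing else. A comparison of logged worsening between arms would mix a true difference with a difference in opportunity to be recorded. The likely direction is more recorded events under iCT-SAD + TAU.

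2. **An equal measure left unused.** The LSAS is collected on one schedule in both arms and the protocol has a threshold for a reliable rise, yet a rise past that threshold does not by itself enter the adverse-event log or its review. With no visit stated for deterioration, a week-8 rise may or may not count, and it matters most for someone who later gives no week-15 score.

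At stake is the between-arm description of the first-listed harm. The primary efficacy analysis is not affected.

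**Working it through.** **Side-by-side reading**

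| Feature | Worsening as adverse event ({22}) | Reliable deterioration (Response to treatment) |
|---|---|---|
| Criterion | none stated | LSAS rise of 12 points or more |
| Source, iCT-SAD + TAU | therapist and checklist | LSAS questionnaire |
| Source, TAU alone | checklist | LSAS questionnaire |
| Visits | during treatment; checklist with the assessment packs | not stated |
| Reference to the other | none | none |

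The left column differs by arm and the right column does not.

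**What follows from the missing visit.** Take a participant whose LSAS is at least 12 points above baseline at week 8.

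- If any visit counts, the participant is deteriorated.
- If only baseline to week 15 counts and week 15 is given, the week-15 score decides.
- If only baseline to week 15 counts and week 15 is missing despite the {18b} invitation, the participant cannot be classified and is not counted. The week-8 checklist or, under iCT-SAD, the therapist log may still hold the event.

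**Size.** The protocol gives no deterioration rate, so there is no stated figure to reproduce on this point. The one usable input is the dropout allowance in Sample size {14}: up to 20%, with 30 per arm.

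- Without week 15 at that allowance: 0.20 × 30 = 6 per arm, 12 of 60.
- At half the allowance: 0.10 × 30 = 3 per arm, 6 of 60.
- Each uncounted case is 1/30 = 3.3 percentage points of an arm.

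The rest is assumption. Let r be the deterioration rate among those with week 15. Let m be the ratio of the rate in leavers (seen at week 8) to r, and suppose every leaver gave a week-8 LSAS. With 24 completers and 6 leavers per arm:

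- counted = 24 × r
- not counted = 6 × m × r
- share not counted = 6m / (24 + 6m), whatever r is

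| r (assumed) | m (assumed) | Counted | Not counted | Share |
|---|---|---|---|---|
| 5% | 1 | 1.2 | 0.3 | 0.3/1.5 = 20% |
| 5% | 2 | 1.2 | 0.6 | 0.6/1.8 = 33% |
| 5% | 4 | 1.2 | 1.2 | 1.2/2.4 = 50% |

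Over r from 3% to 10% and m from 1 to 4, the expected number not counted runs from 6 × 0.03 = 0.18 to 6 × 0.40 = 2.4 per arm. These figures apply only under the week-15 reading.

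**The case against.** The case on the other side is substantial, and much of it stands.

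- **The threshold is not tied to pre-post change.** A reader might infer that it is, because response and remission both refer to the post-treatment score. The deterioration sentence says nothing of the kind, and the criteria are said to come from a cited pilot trial that is not shown. The baseline-to-week-15 reading is plausible but remains an inference.
- **Leaving is not the same as being lost.** A reader might also infer that anyone who worsens by week 8 and leaves disappears from the harm record. The documents do not support that. Early leavers from either arm are invited to later assessments, the mid-treatment pack carries the negative-effects checklist in both arms, and iCT-SAD therapists review scores. Both arms also see their psychiatrist at least monthly for safety monitoring.
- **There is no contradiction.** A score-based outcome and a reported-harms category can coexist, and different instruments may give different counts.
- **Visits and denominators belong in a SAP.** Their absence from this article would not be a finding by itself.
- **Dramatic contrasts are assumption.** One can set 1/24 = 4.2% against 4/30 = 13.3%, but that needs 3 of 6 leavers (50%) to have deteriorated, twelve times the 1/24 in completers. Nothing in the protocol supports such a ratio.

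What the objection does not remove is the difference in detection. How an adverse event is ascertained is a matter of trial conduct, fixed in the harms section, and that section gives one arm a route the other lacks while the equal measure goes unused. The monthly psychiatrist visits do not close this gap, because the harms section does not name psychiatrists as a source for the log.

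**Conclusion.** The point holds as an optional, inexpensive improvement. Established from the text: ascertainment of symptom worsening differs by arm, the LSAS and the 12-point threshold are not linked to it, and the deterioration sentence names no visit. Conditional: a week-8 rise goes uncounted as deterioration only if the definition is read as baseline to week 15 and the participant also gives no week-15 LSAS. Even then, the worsening may be on record through the checklist or the therapist.

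The number affected is unknown. At the 20% planning allowance at most 6 of 30 per arm would lack week 15, and only those among them with a qualifying week-8 rise matter. The range of about 0.2 to 2.4 per arm rests wholly on the assumed rates above. The allowance is itself a planning figure, so actual attrition could be lower or higher.

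**What to change.** 1. In Response to treatment, or in the SAP, state the visits for deterioration. Report by arm, with one rule for both arms, the number with an LSAS at least 12 points above baseline (a) at week 15 and (b) at week 8 or week 15. Use all randomised participants as denominator and show separately those with no post-baseline LSAS.
2. In Adverse event reporting and harms {22}, add that each such rise in either arm is flagged under the symptom-worsening category, marked as LSAS-derived so that it can be told apart from therapist and checklist reports, and passed to the trial team's existing adverse-event review. This sets no clinical rule.
3. Report week 27 for iCT-SAD + TAU on its own, since TAU alone has no assessment then.

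The cost is about one sentence in each section and one derived variable from data already collected. The downside is that some transient rises, or rises from measurement error, will be counted at week 8. Giving two visits a chance to qualify makes this more likely, which is why both counts are shown.
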